### Study Population and Sampling

The study population includes all adults aged 18 years and older who are usual residents in the defined rural and urban HDSS areas (ie, the 4 selected wards) at the time of the baseline census. For operational purposes, a “usual resident” is defined as an individual who has lived in the household for at least 3 of the previous 6 months or who intends to stay for at least 6 months, consistent with HDSS standards. As an HDSS, the system aims for exhaustive inclusion of all eligible adults within the mapped households rather than a sample-based design.

Within each mapped household (HHID), fieldworkers use a standardized roster module on the tablet to list all household members, recording name, sex, age, relationship to head of household, and residency status. Adults (aged ≥18 y) who meet the residency criterion and provide informed consent are included and invited to complete individual-level interviews and measurements. Exclusion criteria are (1) individuals younger than 18 years; (2) visitors or short-term guests who do not meet the residency definition; (3) individuals who are unable to provide informed consent and for whom no appropriate consenting procedure is approved; and (4) individuals who explicitly decline participation. For temporarily absent eligible adults (eg, at work or school), at least 2 repeat visits are scheduled at different times and days before classifying them as nonresponders for that round. This approach ensures near-complete coverage of the adult resident population in both communities.

Within the 4 selected wards, all mapped households constitute the sampling frame, from which a systematic sample of households is drawn. Within each sampled household, all adults aged 18 years and older who meet the residency criterion are identified and invited to participate. Although the HDSS does not enroll every eligible adult resident because of resource constraints, this probability-based household sampling strategy, combined with formal power calculations, ensures that the resulting sample size is sufficient to address the primary study objectives. Using a baseline hypertension prevalence estimate of 30%, consistent with published data from Zimbabwe and comparable sub-Saharan African settings, a margin of error of ±2%, a 95% CI, and a design effect of 1.5 to account for household clustering, a minimum sample of approximately 3000 adults per site is required for robust prevalence estimation. This yields a total minimum analytical sample of 6000 adults across both rural and urban sites.

For the detection of a modest 2% absolute annual change in hypertension or diabetes prevalence (eg, from 30% to 32%) between surveillance rounds, with 80% statistical power and a 2-sided α of .05, a minimum of approximately 3500 participants per site per round is required. The estimated adult population across the 4 HDSS wards substantially exceeds this threshold, supporting the longitudinal objectives of the study. For rural-urban comparative analyses, equal allocation across the 2 sites provides 80% power to detect an absolute difference of 3% to 5% in key NCD outcomes. Subgroup analyses by sex, age group, and socioeconomic stratum are designated as exploratory, and appropriate corrections for multiple comparisons will be applied. Sample size calculations were performed in accordance with the WHO STEPwise approach to NCD risk factor surveillance (WHO STEPS) sample size guidance for population-based NCD surveys.

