**Methods:**

The HDSS uses a stratified multistage sampling design to recruit adults (aged ≥18 y) residing across 2 rural and 2 urban wards. Initial activities include comprehensive community profiling and household mapping, followed by a rigorous baseline survey, with systematic follow-ups scheduled every year. Data encompass essential domains such as vital events, migration patterns, detailed social determinants of health, health behaviors, self-reported and clinically assessed NCDs, physical examinations (including height, weight, blood pressure, and waist/hip circumference), biochemical markers (fasting glucose, lipid profiles, and urine sodium/creatinine), and standardized verbal autopsies. Data capture will make use of REDCap (Research Electronic Data Capture) to facilitate real-time data entry and validation. The protocol is underpinned by rigorous quality assurance procedures, continuous community engagement, and comprehensive ethical oversight.

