### Study Setting

The HDSS implementation will occur across 2 purposively selected districts within Mashonaland Central Province, Zimbabwe: Mt Darwin (rural site) and Bindura (urban site). Mt Darwin District encompasses approximately 1500 km^2^, hosting an estimated population of around 120,000 residents. The population predominantly relies on subsistence and small-scale commercial farming (eg, maize and tobacco), with sociodemographic indicators suggesting moderate educational attainment and agriculture-based household income. Health care services are provided by the Mt Darwin District Hospital and smaller rural clinics. Bindura District represents the urban setting, covering roughly 2800 km^2^ with an estimated population of 140,000 distributed across 14 wards. Bindura exhibits higher population density and a diversified economy, including mining (Bindura Nickel Corporation), trading, and academic communities linked to Bindura University. Health infrastructure is comparatively advanced, featuring the Bindura Provincial Hospital (a 200-bed referral facility) complemented by an extended clinic network. The HDSS will utilize 4 purposively selected wards (2 rural and 2 urban) to capture these socioeconomic and epidemiological contrasts.

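### The protocol describes both full inclusion of eligible adults and a systematic household sample, which leaves coverage misstated and the base for vital and incidence rates undetermined

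*Protocol article*

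**What the plan says.** All quotes here are from the protocol article, section Study Population and Sampling.

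- **Full inclusion (first two paragraphs).** The text says that "the system aims for exhaustive inclusion of all eligible adults within the mapped households rather than a sample-based design". It continues: "Within each mapped household (HHID), fieldworkers use a standardized roster module on the tablet to list all household members". Adults found this way who meet the residency rule and consent are invited to interview and measurement. The second paragraph closes: "This approach ensures near-complete coverage of the adult resident population in both communities".
- **Sampling (third paragraph).** Within the four wards, "all mapped households constitute the sampling frame, from which a systematic sample of households is drawn". The same paragraph concedes that "the HDSS does not enroll every eligible adult resident because of resource constraints" and then gives a precision-based minimum of about 3000 adults per site.

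Other sections bear on the base for rates. Community Profiling and Household Mapping gives an HHID to every structure that meets the household definition. Data Collection Methods links births, deaths and migrations to each HHID. Follow-Up Procedures sends teams back to each HHID and enrols new residents found in any previously mapped household. Data Analysis announces birth, mortality, prevalence and incidence rates without naming their base.

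**The concern.** The first description does not merely leave sampling out; it denies it. The third paragraph's remark about limited resources therefore cannot be read as a refinement of the earlier text.

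Two things are at stake. First, the coverage claim: if the third paragraph describes what was done, the article claims a property that the cohort does not have. Second, the rates. If baseline adults come from sampled households while events and in-migrants are picked up in all mapped households, numerators and person-time can come from different sets of households. A mortality, migration or incidence rate built that way has no defined population.

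**Working it through.** **1. Which design does the sample size assume?**

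Inputs, all from Study Population and Sampling: prevalence p = 0.30, margin d = 0.02, 95% confidence (z = 1.96), design effect 1.5 for household clustering.

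- Simple random sample: n = z² p(1−p) / d² = 1.96² × 0.3 × 0.7 / 0.02² ≈ 2017.
- With the design effect: 1.5 × 2017 ≈ 3025.

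The plan's figure of about 3000 per site is reproduced. It is a sample-survey calculation and fits the third paragraph, not a design that aims to include everyone.

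**2. The two household sets side by side**

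| Item | Full-inclusion text | Sampling text |
|---|---|---|
| Baseline adults | all mapped households | sampled households only |
| Roster at baseline | each mapped household | not stated |
| Vital events and revisits | each HHID, so all mapped households | not restricted to sampled households |
| In-migrants enrolled | any previously mapped household | not restricted to sampled households |
| Base for rates in Data Analysis | not stated | not stated |

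Under full inclusion, every row refers to the same households. Under sampling, the first row shrinks while the event, revisit and in-migrant rows, as written, do not.

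**3. Illustration of coverage (not a measurement)**

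Study Setting gives Bindura an estimated 140,000 people in 14 wards. The size of the two selected wards is not given, so average size is assumed. An adult share of 45%–60% is also assumed.

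- People in two average wards: 2 × 140,000 / 14 = 20,000.
- Adults: 20,000 × 0.45 = 9000 to 20,000 × 0.60 = 12,000.
- Share enrolled at the stated minimums of 3000 and 3500 per site: 3000 / 12,000 = 25% to 3500 / 9000 = 39%.

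With a wider assumption of 5000 to 20,000 adults per site, 3000 enrolled would be 60% down to 15%.

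**4. Illustration of a mismatched base**

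If events were counted in all mapped households and person-time only in sampled ones, a rate would be overstated by roughly the ratio of all adults to enrolled adults. Under the assumptions of step 3 that is 9000 / 3500 ≈ 2.6 to 12,000 / 3000 = 4.0. Under the wider assumption with 3000 enrolled it is about 1.7 to 6.7. The protocol does not say that rates will be computed this way; it does not rule it out.

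**The case against.** The best defence is a two-tier reading: every mapped household is rostered and followed for births, deaths and migration, and only a sample of households is interviewed and measured. The HHID wording supports this, and vital rates would then rest on the whole register. The defence has force. It means that a reader who infers that vital events come only from sampled households goes further than the text. It does not remove the contradiction, because the full-inclusion paragraphs invite adults from mapped households to interview and measurement, and no section states a two-tier design.

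Other stronger readings also fail:

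- **Three incompatible designs.** The Abstract says "The HDSS uses a stratified multistage sampling design to recruit adults". With purposively chosen wards (Study Setting) and one described probability stage, the label is inaccurate. It can still be read loosely as rural and urban strata, then wards, then households, so it is a mislabel and not a clear third design. The comprehensive enumeration praised under Strengths and Limitations may refer to the door-to-door listing, which is complete under either design.
- **Contradictory weighting.** No section mentions weights. A census needs none; a sample may need them. A single systematic draw across a site's list would be about self-weighting, and the text does not say whether the draw was made ward by ward. Weighting is undetermined, and an article may leave such detail to a fuller document.
- **Coverage figures as estimates.** The 3000 and 3500 are minimums, not achieved enrolment, and a district average may not fit two selected urban wards. Nothing comparable can be derived for Mt Darwin, because its number of wards is not given.

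**Conclusion.** The contradiction over coverage is firm. It lies within one section of current text and depends on no assumption. The sample-size calculation, reproduced at about 3025, fits sampling. If the third paragraph is what was done, the denial of a sample-based design and the claim of near-complete coverage are wrong as written.

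It follows that the base for birth, death, migration and incidence rates is undetermined. It is not shown to be wrong: the documents do not establish that vital events come from sampled households only, or that any rate will mix two household sets.

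The 25%–39% coverage and the rate ratios of 2.6 to 4.0 only illustrate the possible size. They rest on average ward size, an assumed adult share and minimums treated as enrolment.

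**What to change.** State once the design used at baseline, which was completed in December 2024 (Mt Darwin) and March 2025 (Bindura): which households were rostered, which were sampled for interview and measurement, and which base each rate uses. Delete the description that does not apply.

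If the third paragraph is what was done:

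- remove the denial of a sample-based design and the near-complete coverage claim;
- in the Abstract, replace the stratified multistage label with: systematic household sample within four purposively selected wards;
- restrict in-migrant enrolment and person-time to the household set that supplied the baseline cohort, or report vital rates from the full register separately;
- if sampling fractions differ between wards, weight site estimates by the inverse fraction and give household-clustered intervals.

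The cost is text changes, a less favourable coverage claim and a little more analysis. The documents do not show whether ward sampling fractions were recorded, so this should be checked first. The rule on in-migrants should be settled before the first follow-up round, planned for the second quarter of 2027, and the coverage wording before the baseline results are submitted.

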### Follow-Up Procedures

Following the baseline census, longitudinal data collection rounds will be implemented annually over the 5-year surveillance period. Using the existing household and individual registers, field teams revisit each HHID and reverify the household roster, updating entries for births, deaths, in-migrations, out-migrations, and changes in marital status. Migration events are classified and dated using standard HDSS definitions, enabling calculation of person-time at risk and net migration rates. Migration events are identified and documented during each annual household roster update. New residents found in a previously mapped household who meet the standard residency criterion (at least 3 of the last 6 mo or intending to stay at least 6 mo) are classified as in-migrants, assigned a unique individual ID, and enrolled prospectively, with their origin and date of arrival recorded. Previously enrolled individuals confirmed by household members to have permanently departed the HDSS ward boundaries are classified as out-migrants, with their date of departure, destination, and reason for migration recorded and their follow-up record closed from that date, contributing person-time up to departure. Individuals who return after out-migration are reenrolled under their original ID, ensuring longitudinal continuity.

At each round, eligible adults are recontacted for updated interviews and measurements to estimate NCD prevalence and incidence, monitor changes in health-related behaviors and attitudes, and track risk factors over time. All recorded deaths are subjected to verbal autopsy using the WHO 2016 [31] standardized instrument administered on tablets; data are processed with automated cause-of-death assignment tools (eg, InterVA or InSilicoVA), given the limitations of vital registration in this setting.

Participant retention is managed through a structured recontact protocol whereby temporarily absent individuals receive at least 2 repeat visits at different times before being recorded as noncontactable for that round. At each round, the baseline characteristics of participants lost to follow-up will be compared with those retained to assess and account for potential attrition bias.

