### Data Analysis

The analytic plan encompasses descriptive statistics, robust prevalence and incidence estimations, and comparative analyses designed to quantify rural versus urban differences. Statistical software, primarily Stata (version 18; StataCorp LLC), will be employed. Numeric variables will be summarized using medians and IQRs, while categorical variables will be summarized using proportions. Logistic regression analyses (univariable and multivariable) will be used to identify and assess risk factors associated with NCDs, employing a hierarchical approach and stepwise backward elimination. The calculation of birth, mortality, prevalence, and incidence rates will be executed accordingly, and chi-square tests for trend will be used to analyze changes in NCD burden over time. Advanced statistical techniques, including regression and survival analyses, will facilitate robust estimation of NCD determinants and epidemiological transitions between the distinct study settings.

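### The 3500 per site per round does not follow from its own inputs: a 2-point hypertension difference between two independent rounds needs about 8,390 for 80% power

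*Protocol article*

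**What the plan says.** Study Population and Sampling gives two calculations in sequence. The first is for the precision of a single-round prevalence: 30% hypertension, a margin of ±2 points, 95% confidence and "a design effect of 1.5 to account for household clustering", leading to about 3000 adults per site.

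The second is for change over time. Its target is the "modest 2% absolute annual change in hypertension or diabetes prevalence (eg, from 30% to 32%) between surveillance rounds". Power is set at 80% and the test is two-sided at the 5% level. The result is that "a minimum of approximately 3500 participants per site per round is required". This sentence names no formula, design effect, pairing, within-person correlation or retention.

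Two other sections bear on it. Follow-Up Procedures says that the same people are seen again: "At each round, eligible adults are recontacted for updated interviews and measurements to estimate NCD prevalence and incidence". Data Analysis says that "chi-square tests for trend will be used to analyze changes in NCD burden over time".

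**The concern.** The second calculation prints everything a two-proportion sample size needs, so it can be checked directly. A 2-point difference near 30% is small relative to binomial variation, and 3500 per round looks far too few. The adjacent sentence adds to the doubt: for rural-urban comparisons the article claims 80% power only for differences of 3 to 5 points.

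Temporal trends are part of the second of the article's four study aims, and the section relies on its power calculations to call the sample sufficient for the primary objectives. If the 2-point claim is taken at face value, a non-significant difference between two rounds at one site could be read as evidence of stable hypertension prevalence when the comparison had less than an even chance of showing the change.

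**Working it through.** **Inputs.** From Study Population and Sampling: p1 = 0.30, p2 = 0.32, two-sided alpha 0.05 (z = 1.96), power 80% (z = 0.8416), 3500 per site per round, design effect 1.5 (stated for the precision calculation only). From the Introduction: diabetes 5.7%.

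**1. The adjacent figure reproduces.** 1.5 × 1.96² × 0.30 × 0.70 / 0.02² = 3,025, which matches the stated 3000.

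**2. The 3500 does not.** For two independent samples:

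n = (1.96 + 0.8416)² × (0.30 × 0.70 + 0.32 × 0.68) / 0.02² = 7.849 × 0.4276 / 0.0004 ≈ 8,390 per site per round.

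This is 8,390 / 3500 = 2.4 times the stated figure. With the design effect it is about 12,590, or 3.6 times.

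**3. Variants.** None gives 3500:

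| Variant | n |
|---|---|
| Pooled variance | 8,394 |
| Continuity correction | 8,493 |
| One-sided test | 6,612 |
| Fall from 30% to 28% | 8,080 |
| One sample against a fixed 30%, two-sided | 4,165 |
| One sample against a fixed 30%, one-sided | 3,285 |

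**4. Power at 3500, 30% vs 32%.**
- No design effect: 0.02 / √(0.4276/3500) − 1.96 = 1.81 − 1.96 = −0.15, so 44%.
- Design effect 1.5 (effective n = 3500/1.5 = 2,333): 1.48 − 1.96 = −0.48, so 31%.
- Both sites pooled (7000 per round): 73%, or 55% with the design effect.

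**5. Detectable change at 3500 with 80% power, starting from 30%.** About 3.1 points, or about 3.8 points with the design effect.

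**6. Diabetes, 5.7% to 7.7%.** About 2,453 per round are needed. Power at 3500 is 92%, or 78% with the design effect.

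**7. What pairing would require.** If the same adults are compared with full retention, n ≈ 8,390 × (1 − ρ), where ρ is the within-person correlation. Reaching 3500 needs ρ = 1 − 3500/8,390 = 0.58. With the design effect it needs ρ = 1 − 3500/12,586 = 0.72. The article gives no ρ, so this table shows a range of assumed values (paired McNemar test at 3500):

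| Assumed ρ | Power | Power with design effect 1.5 |
|---|---|---|
| 0.3 | 58% | 42% |
| 0.5 | 73% | 55% |
| 0.7 | 91% | 77% |

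**8. A sustained rise of 2 points a year.** The Results section puts the end of baseline at December 2024 and March 2025, the first follow-up in the second quarter of 2027, and annual rounds through 2029.
- The first follow-up comes a little over two years after baseline, so the expected difference is at least 4 points. For 30% vs 34% at 3500, power is 95%, or 83% with the design effect.
- For a linear trend over four independent rounds at about 0, 2.25, 3.25 and 4.25 years, the times have mean 2.44 and sum of squares 9.92, and the mean prevalence is 0.349. Then z = 0.02 × √(3500 × 9.92 / (0.349 × 0.651)) ≈ 7.8, or 6.4 with the design effect. Power exceeds 99% in both cases.

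**The case against.** Three objections carry weight.

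**The same adults are recontacted.** Independent-sample power is therefore not the only possible reading, and under a paired analysis the true power is unknown. That stands as a condition on the 44% and 31%. It does not rescue 3500, which would need full retention and a correlation of 0.58 or more (0.72 with the design effect). The article states neither. Its limitations section expects loss to follow-up, and the test it names for change over time does not use pairing. Data Analysis also mentions regression and survival methods, but ties none of them to this calculation.

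**The design effect is carried over.** The article gives 1.5 for single-round precision, and the inflation for change within the same households need not be 1.5. This stands: the figures of 31%, about 12,590 and 3.8 points are conditional on that assumption. The figures without it already show the shortfall.

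**The consequence is limited.** A reader might infer that the study would miss a real upward trend in hypertension. The documents do not support that. The target is an annual change, the first follow-up comes more than two years after baseline, and the planned test is for trend over several rounds. On that schedule a sustained 2-point annual rise would very probably be found. A reader might also extend the error to diabetes, but at 5.7% the 3500 is adequate without the design effect and close to adequate with it.

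Finally, 3500 is a stated minimum and the enrolled number is not given, so achieved power may differ. The sentence still ties 3500 to 80% power, and that link is wrong.

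**Conclusion.** The point holds in a limited form. As printed, 3500 per site per round is too small by a factor of about 2.4 for 30% versus 32% with 80% power at a two-sided 5% level, or about 3.6 with the design effect. Power at that size is about 44%, or 31%. This rests on treating the rounds as independent samples, which fits the printed inputs and the named trend test, and, for the second figure in each pair, on applying the 1.5 to change as well as to precision. The scope is a 2-point hypertension difference between two rounds at one site; the multi-round trend and the diabetes example are not undermined.

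**What to change.** Correct the sentence in Study Population and Sampling in one of three ways.

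1. **Restate the detectable change.** Say that at 3500 per site per round, with rounds treated as independent samples, the between-round change in hypertension detectable with 80% power from 30% is about 3.1 points, or about 3.8 points with a design effect of 1.5. State diabetes separately with its own starting prevalence; from 5.7%, a 2-point rise has about 92% power (78% with the design effect).
2. **Give a paired-panel calculation.** State the assumed within-person correlation, retention and design effect, and name an analysis that uses the pairing.
3. **Base the claim on the trend test.** State the number and timing of rounds and the annual slope to be detected, since this is the test named for change over time.

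The cost is rewording one paragraph; the second option also needs a matching change in Data Analysis. No extra enrolment is needed, and no follow-up round has yet been run. Under the first option the stated detectable change becomes less favourable.
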